##### Dosing parameters

*Opioid therapy*

Pharmacologic treatment regimens vary greatly among clinical sites treating NOWS [6, 7]. While morphine remains the most commonly used agent [8], the individual drugs, initial and maximum doses, and weaning rates are not standardized. In addition, some sites use a fixed percentage up titration rate independent of symptom scores, while others use a non-weight-based dose titration rate driven by score severity. Neither of these two approaches have been standardized, nor is there evidence of the superiority of either approach [9]. The dynamic nature of dosing based upon a disease severity score provides significant protection against excess dosing and respiratory depression in the highly monitored settings in which NOWS is treated, particularly during the intensive up titration phase until capture of scores is obtained. Excess sedation will be evident before respiratory depression emerges. Study sites all have well developed internal protocols for dosing that have evolved over many years, as well as robust monitoring procedures with discretion of caregivers to hold doses based upon clinical presentation of the infants. These make AEs of excess sedation from opioids exceeding uncommon during routine clinical care. There have been pharmacokinetic investigations to explore dose optimization [10–14], but none has been extensively tested and validated. These factors and the use of a crossover design favor the use of site-specific regimens in a comparative effectiveness approach rather than a uniform dosing approach. Minimum dosing intervals (i.e., time between doses) for each opioid type have been developed by the study team and should be considered when developing the symptom-based dosing algorithm at each study site. All study sites will adhere to the following broad dosing parameters (see Table 1).

**Table 1 Tab1:** Opioid therapy dosing parameters

	Morphine	Methadone	Buprenorphine
Minimum initial dose	0.05 mg/kg	0.1 mg/kg	4.5 mcg/kg
Maximum daily dose	1.6 mg/kg/day	0.6 mg/kg/day	75 mcg/kg/day

*Adjunctive secondary and tertiary medications*

An evidence-based choice of optimal secondary medication is also not defined in the literature. Though doses are largely empirically derived, extrapolated from adults, or in the case of phenobarbital extrapolated from use in seizure control, there is a greater convergence upon a more standardized dose regimen than with opioids. All study sites will adhere to the following broad dosing parameters (Table 2).

**Table 2 Tab2:** Secondary and tertiary medication dosing parameters [15]

	Phenobarbital	Clonidine
Maximum loading dose	20 mg/kg	N/A
Minimum initial dose	1.25 mg/kg/day	0.625 mcg/kg
Maximum daily dose	5 mg/kg/day	24 mcg/kg/day

All enrolled infants will be assessed at 3 months of age for the use of nonscheduled medical care which includes acute/urgent care visits, emergency room visits, and hospital readmissions. This assessment will include a review of the medical records which will include data from the hospital in which the infant was born, and any additional information that can be assessed through linked medical records.

All enrolled infants will be assessed for seizures and death until hospital discharge.

All enrolled infants will also be assessed for non-accidental trauma or death at 3 months of age. These assessments will include a review of the medical records including data from the hospital in which the infant was born, and any additional information that can be assessed through linked medical records, in addition to a review of public facing media.

### Primary endpoint

Time from birth until infant meets criteria for medically ready for discharge (days). An infant is considered medically ready for discharge when they are discharged by the medical provider or when they meet both of the following criteria:≥96 h of age≥48 h since last dose of opioid treatment (i.e., morphine, methadone, or buprenorphine)

### Secondary endpoints

All enrolled infants:Receipt of pharmacologic treatment (yes/no)Time from birth until hospital discharge (days)Inpatient composite safety outcome (present/absent)◦ Seizures◦ Excessive weight loss more than 15% from birthweightInpatient composite critical safety outcome (present/absent)◦ Non-accidental trauma◦ DeathOutpatient composite safety outcome (present/absent)◦ Acute/urgent care or emergency room visits◦ Hospital readmissionsOutpatient composite critical safety outcome (present/absent)◦ Non-accidental trauma◦ Death

Among all enrolled infants who were pharmacologically treated:Number of doses of primary medication administered (count)Receipt of secondary medications (yes/no)Inpatient composite safety outcome (present/absent)◦ Seizures◦ Excessive weight loss more than 15% from birthweightInpatient composite critical safety outcome (present/absent)◦ Non-accidental trauma◦ DeathOutpatient composite safety outcome (present/absent)◦ Acute/urgent care or emergency room visits◦ Hospital readmissionsOutpatient composite critical safety outcome (present/absent)◦ Non-accidental trauma◦ Death

Among all enrolled infants who were initially pharmacologically treated with a symptom-based dosing approach:Transition to an opioid taper due to persistent signs of withdrawal (yes/no)

Among all enrolled infants who were initially pharmacologically treated with a scheduled opioid taper approach:Cessation of opioid treatment due to excessive sedation or respiratory depression (yes/no)

### Stratification, randomization, and blinding/masking

Each study site (i.e., cluster) will be randomized in a 1:1 allocation ratio to one of two sequences, following a 5-week run-in:Scheduled opioid taper approach for 5 months (period 1) followed by a 3-week washout followed by symptom-based dosing approach for 5 months (period 2)Symptom-based dosing approach for 5 months (period 1) followed by a 3-week washout followed by scheduled opioid taper approach for 5 months (period 2)

The randomization scheme will be stratified by the assessment and management approach used at each study site (i.e., FNAST or ESC). Study sites will be notified of their allocated sequence following randomization.

Due to the nature of the study intervention, the protocol study team, site PI, site study team, and participants will be unblinded to the assigned study intervention.

## Participant selection

### Study setting

At least 24 sites from varying geographic areas in the USA will be selected for participation in this study and will include community hospitals, academic hospitals, and regional pediatric referral centers.

### Inclusion criteria

Sites who meet all of the following criteria are eligible to participate in this study:The site is willing and able to transition to a symptom-based dosing approach at a randomly allocated time and is willing and able to transition from a symptom-based dosing approach to a scheduled opioid taper approach at a randomly allocated time.The site uses either the Eat, Sleep, and Console care approach or the Finnegan Neonatal Abstinence Scoring Tool or modification thereof to assess infants with NOWS and will continue to use the same assessment and management approach throughout the study.The site provides scheduled opioid treatment with morphine, methadone, or buprenorphine for infants with NOWS and has an established algorithm for a scheduled pharmacologic taper prior to study initiation. The site agrees to maintain the type of opioid(s) used and use the study approved treatment algorithms throughout the study.

Individuals who meet all the following criteria are eligible for enrollment as study participants:The infant is ≥ 36 weeks’ gestation.The infant had antenatal opioid exposure identified by at least one of the following:◦ History of maternal opioid use during pregnancy◦ Positive maternal toxicology screen for opioids during the second or third trimester of pregnancy◦ Positive infant toxicology screen for opioids during the initial hospital stayThe infant is being assessed and managed for NOWS at an eligible study site.The infant is at risk for pharmacologic treatment for NOWS defined by either of the following:◦ At least 1 score ≥ 8 if assessed and managed with FNAST or modification thereof◦ At least 1 yes if assessed and managed with the ESC care approach

### Exclusion criteria

Sites who meet any of these criteria are not eligible to participate in this study:The site manages less than 5 infants who receive pharmacologic treatment for NOWS annually.The site routinely discharges/transfers infants from the hospital on opioid treatment (i.e., morphine, methadone, or buprenorphine). Routine is defined as ≥ 10% of infants who receive opioid treatment for NOWS at the time of hospital discharge.The site routinely uses more than one opioid type for the pharmacologic treatment of infants with NOWS. Routine is defined as ≥ 10% of infants who receive more than one opioid for the treatment of NOWS.

Individuals who meet any of these criteria are not eligible for enrollment as study participants:The infant has major birth defect(s).The infant has neonatal encephalopathy (inclusive of hypoxic ischemic encephalopathy), a metabolic disorder, stroke, intracranial hemorrhage, or meningitis diagnosed prior to the initiation of pharmacologic treatment.The infant is receiving respiratory support (any positive pressure or oxygen therapy) at 48 h of age.The infant has undergone major surgical intervention prior to or at 48 h of age.The infant has postnatal opioid exposure prior to the initiation of pharmacologic treatment for NOWS.The infant was outborn and pharmacologic treatment was initiated at the transferring hospital.The infant is assessed for eligibility during the study site’s 3-week washout.

### Recruitment

The protocol study team will screen interested sites for eligibility and will randomize eligible sites into one of two arms (see Fig. 1). With the proposed study design, all infants with NOWS cared for at each study site will be managed using the dosing approach assigned to the study site during one of the two study periods. There will be a 5-week run-in prior to the first study period. There will be a 3-week washout between the end of the first study period and start of the second study period where no infants will be enrolled. Study sites will transition their pharmacologic treatment approach per their randomized allocation during the 3-week wash out period. The inpatient clinical team will assess infants with antenatal opioid exposure and establish the diagnosis of NOWS. The initiation of clinical management for infants with NOWS will not be impacted by the study intervention. Non-pharmacologic care will be considered first-line treatment for all infants with NOWS at study sites and will be implemented and maximized per each study site’s usual approach. The site study team will identify potential participants based on their eligibility following review of the medical record after delivery.

Site recruitment and retention: The protocol study team began to optimize the potential for recruitment during initial protocol development through an assessment of potential study sites’ willingness to participate in and enthusiasm for various study designs. The study design chosen for this protocol incorporates feedback from potential sites. During the site assessment process, the protocol study team will expect each site to commit in writing to the site’s participation in and completion of the study with maintenance of the site’s allocated study intervention for the duration of the study. The protocol study team will facilitate retention of study sites through the focused allocation of funds to support participation, assessment of needs, provision of support, and troubleshooting at each study site, as needed.

## Known and potential risks and benefits

### Potential risks

Under the proposed study design, all infants managed for NOWS at a study site will receive care consistent with the pharmacologic approach assigned by the protocol study team. Sites throughout the country are currently using both dosing approaches described in this study. Use of either pharmacologic approach will not expose infants in this study to risk beyond that of usual/accepted clinical care. This is minimal risk research. Clinical experience and pharmacokinetic investigations provide assurance of the safety of three symptom-driven administrations of a fixed low dose every 1 to 2 h for morphine, methadone, and buprenorphine. Systemic drug exposure of morphine, methadone, or buprenorphine will not extend beyond that seen in usual clinical care for NOWS [10, 16–18].

Involvement in the study will not increase the risk to the family of legal ramifications associated with the in utero opioid exposure of their infants, as only infants who are diagnosed with and being actively managed for NOWS will be screened for enrollment in the study. There will be no additional toxicology screening (maternal or infant) performed beyond what medical professionals would typically obtain as part of usual institutional care at the study site. Thus, there will be no additional information garnered with respect to substance use during pregnancy due to involvement in the study. As an NIH-funded investigation, this study has the default protections of a Certificate of Confidentiality for all sensitive patient information.

Children in the study and their mothers will have medical records reviewed by study personnel. This is a small risk of loss of confidentiality of medical record information. All data files will be coded in a manner that makes identification of the subjects unlikely. Subjects’ identification codes are simply their numerical enrollment in the study and thus do not lend themselves to inadvertent or unauthorized identification of subjects. Transmission of electronic records will be over a secure encrypted connection and will not contain Protected Health Information (PHI). Only coded data will be transmitted and maintained at the DCC.

### Potential benefits

There is equipoise about the optimal dosing approach, and using a cluster crossover design, all infants at a study site will receive the same dosing approach during a set study period. There is empirical evidence that infants enrolled in clinical trials have better outcomes than similar infants treated outside of a clinical trial [19], and that the outcomes of all infants are better at centers that routinely conduct clinical trials. Within the context of NOWS therapeutics, there is evidence of the benefit of a uniform and protocol-driven approach to therapeutics which will be a key element of this clinical trial. Thus, it is likely that the care of infants at all study sites will be improved, regardless of the specific study period during which they are enrolled [20].

## Study procedures and data collection

### Study assessments/evaluations

A summary of complete study procedures is detailed in the study schedule. Details of each assessment are provided below.

#### Among all screened infants

Maternal race and ethnicity will be assessed on all screened infants.

#### Among all enrolled infants

The following data, where available, will be collected on all enrolled infants:Study participant demographics including sex, date and time of birth, gestational age at birth, birthweight, length at birth, and head circumference at birthMaternal date of birth, marital status, level of education, medical insurance, and zip code (which will be converted to a rural–urban community area (RUCA) code for analysis), medical history during pregnancy and at delivery, and exposures during pregnancyNeonatal toxicology after birthReceipt of pharmacologic treatment for NOWSAssessment and management approach, including ESC or FNAST assessments/scoresDaily weight from birth to hospital dischargeLocation of care in the hospitalDate and time of hospital dischargeIncidence of death until hospital dischargeSafety outcomes (see sections on collection and reporting of adverse events)

#### Among all enrolled infants who were pharmacologically treated

The following data will be collected on all enrolled infants who were pharmacologically treated during the initial hospitalization following birth:Each type and dose of opioid treatment (morphine, methadone, buprenorphine) prior to hospital dischargeEach type and dose of adjuvant therapy (clonidine or phenobarbital) prior to hospital dischargeDaily feeding information, including type of enteral feedings including formula type, route of administration, and caloric content, from birth to hospital discharge

### SPIRIT figure: OPTimize NOW study events

[figure not shown]

### Data collection methods

Data collected will be from the infant and maternal medical records, including transfer records. All clinical data collected from this study will be extracted directly from the electronic health records or source documents. There will be no interactions with, nor will there be any information collected directly from, the mother, the infant, or the treating clinician.

The site research team will assess the outpatient composite safety outcome as well as the outpatient critical safety outcome through review of the medical records (including the study site’s primary and any linked electronic medical record systems) and media review (public facing) for all enrolled infants at approximately 3 months of age.

## Criteria for participant and study completion and premature discontinuation of study intervention and study termination

### Participant completion

Participant completion will be at 3 months of age.

### Participant stopping rules and withdrawal criteria

Participants may be prematurely terminated from the study for the following reasons:The participant dies.The PI no longer believes participation is in the best interest of the participant.If the family requests that data not be collected on their infant.

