The justification for a waiver of informed consent from caregiver(s) for the previously outlined study objectives meets the above criteria as follows:The research involves no more than minimal risk to the participants.Both approaches to pharmacologic treatment (i.e., the symptom-based dosing approach and scheduled opioid taper approach) are currently used at sites across the country, and the optimal approach to pharmacologic treatment for infants with NOWS is unknown. The protocol study team has utilized recommendations from the AAP to define the primary outcome to further facilitate safe discharge practices for all infants with NOWS. Undertreatment and overtreatment will be minimized by the study parameters developed by the protocol study team and a DSMB will be engaged to identify any risk concerns throughout the study. The usual approach to management of NOWS is protocol-driven based upon a site level therapeutic approach. Dosing approach (symptom versus scheduled) is not decided at the level of the individual patient nor at the discretion of an individual practitioner. Thus, the role of removing individual physician discretion for specific infants, a commonly cited criteria against waiver of consent, is not an issue in NOWS in which dosing approach is determined at the facility level. This clinical trial will employ two widely accepted dosing approaches. In addition, the treatment of NOWS in the inpatient setting is extremely safe regardless of the opioid employed or dosing regimen. This is due to drug dosing that is directly tied to symptom scores every 4 h, signs of excess sedation being evident much before respiratory depression, and careful respiratory monitoring in an inpatient setting.The waiver or alteration will not adversely affect the rights and welfare of the participants.As the best pharmacologic management for infants with NOWS is unknown, there is no universally accepted standard approach, and both management strategies are currently being used at sites across the country. Therefore, participants receiving care via either approach to pharmacologic treatment should not have their rights and welfare adversely affected.The site research team could not practicably carry out this trial without the waiver or alteration.Recent clinical trials in NOWS for which individual patient consent to an altered therapeutic regimen (NCT04214834, 04104646) have encountered a patient consent rate of only 20–30% of those eligible. Though the patient parental characteristics of those who have declined participation cannot be collected in systematic fashion, clinical trialists at these sites have noted those declining tend to have more polysubstance abuse, have higher use of prescribed benzodiazepines and psychotropics, are less likely to be in an outpatient opioid use disorder program, and often have impulse control as part of a comorbid psychiatric diagnosis. Most of these factors have been linked to worse outcomes (as measured by symptom scores and length of treatment for infants). Large (for NOWS) randomized trials with individual level consent have all tended to have enrolled mothers with less of the risk factors listed above [22–24]. The feasibility and generalizability of this trial would be limited if obtaining informed consent were required. It is highly possible that infants with antenatal exposure to illicit or misused opioids may respond differently to symptom-based dosing approach than infants with antenatal exposure to medications for opioid use disorder (MOUD). The goal of this research is to identify a generalizable approach to pharmacologic treatment for infants with NOWS. Enrolling only a consented population will likely bias the study results towards infants born to women who are stable on MOUD and miss a high-risk sub-population of infants with NOWS. This could be particularly problematic in this trial where there may be variation in the response to treatment. Each study site will use the assigned approach to care for all infants with NOWS throughout the trial. Therefore, obtaining consent would not alter the care approach used for the infant. Thus, the benefits afforded by using a waiver of consent outweigh the risks to the infant receiving the same treatment.Whenever appropriate the study team will provide participants with additional pertinent information after participation.Throughout the study, the site study team will provide participants with additional pertinent information when appropriate. The site study team will (a) give to the caregiver(s) of all infants with NOWS who are cared for at the study site throughout the study and/or (b) post (as an enlarged copy) in appropriate location(s) readily visible to caregivers. This will fulfill the suggested framework [25] of participants being “provided with a detailed description of the study interventions to which their cluster has been randomized.”

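### A PI's best-interest judgement can terminate an infant from a record-review study, which leaves care unchanged and permits avoidable loss of later safety data

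*Protocol article*

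**What the plan says.** In the protocol article, *Participant stopping rules and withdrawal criteria* opens with "Participants may be prematurely terminated from the study for the following reasons" and gives three: death, "The PI no longer believes participation is in the best interest of the participant", and "If the family requests that data not be collected on their infant". The second has no objective trigger. Only the third is worded as an end to data collection, and nothing says whether record review goes on after the second.

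Other sections describe what participation means for an infant:

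- *Data collection methods*: all clinical data come from records. "There will be no interactions with, nor will there be any information collected directly from, the mother, the infant, or the treating clinician".
- *Waiver of consent for in-hospital participation*: "Each study site will use the assigned approach to care for all infants with NOWS throughout the trial". The same section argues: "Therefore, obtaining consent would not alter the care approach used for the infant".
- *Stratification, randomization, and blinding/masking*: "the protocol study team, site PI, site study team, and participants will be unblinded to the assigned study intervention".
- *Participant completion*: participation ends at 3 months of age, which is when outpatient safety is reviewed.
- *Analysis populations*: the ITT population is all enrolled participants.
- Table 3: for an infant withdrawn before readiness or before discharge, the time endpoint is the number of days to withdrawal. The safety endpoints have no matching rule.

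**The concern.** A best-interest withdrawal clause makes sense where leaving the study takes the participant off a study procedure or treatment. Here it does not. The infant has no study visits, and the dosing approach belongs to the site. What termination can end is observation.

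That matters because the trial is open-label and the hypothesis is that symptom-based dosing shortens time to readiness safely. If infants leave observation on the judgement of someone who knows the assigned approach, their later inpatient events and their 3-month outcomes (acute or emergency visits, readmission, non-accidental trauma, death) may go unrecorded for reasons connected with how they are doing. The waiver of consent was sought partly to avoid losing higher-risk infants from the sample. An open termination rule allows some of that loss back in after enrolment.

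**Working it through.** The point rests on reading the sections together. The plan states no figure to reproduce.

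**1. Does termination change care?** The opening of *Intervention description*, *Recruitment* and the waiver section all say that the assigned approach is used for all infants with NOWS at the site. The bullets under each approach speak of enrolled infants, but nothing provides a different approach for infants who are not enrolled. The waiver section's argument that seeking consent would not alter care applies equally to ending participation. So termination does not change care.

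**2. What does termination end?** Participation consists of record extraction up to the 3-month review, so ending it naturally ends extraction. Table 3 supports this for the time endpoints, where observation is taken to stop at withdrawal. No sentence says so for the safety endpoints.

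**3. Is this consistent with the rest of the plan?** The text after Table 2, *Data collection methods* and *Collection of adverse event assessment and follow-up* all assign safety review to all enrolled infants, and the ITT population is all enrolled. An infant terminated before 3 months cannot both leave the study and have the complete review that these sections promise.

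**4. Could the loss be related to outcome?** The judgement is open, and both the site PI and the protocol study team are unblinded. The rule therefore permits it. That it would happen is an inference.

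**5. How large could it be?** The documents give no withdrawal rate, so the numbers of infants below are assumptions.

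*Safety percentages.* If k of n infants under one approach have unknown status, the true percentage can lie anywhere in a range of width k/n. The planned n per approach is 24 sites × 10 = 240 overall, 16 × 10 = 160 for ESC and 8 × 10 = 80 for FNAST.

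| k | of 240 | of 160 (ESC) | of 80 (FNAST) |
|---|---|---|---|
| 1 | 0.4 points | 0.6 points | 1.3 points |
| 5 | 2.1 points | 3.1 points | 6.3 points |

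*Primary endpoint (ESC).* Withdrawing k infants of one arm on day w, when their true time was T, lowers that arm's mean by k × (T − w)/n. Take n = 160, a mean of 10.5 days, no true effect, and assume T = 20 to 30 and w = 3 to 5.

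- k = 1: from 1 × (20 − 5)/160 = 0.09 to 1 × (30 − 3)/160 = 0.17 days. The apparent ratio is 0.99 to 0.98.
- k = 5: from 5 × 15/160 = 0.47 to 5 × 27/160 = 0.84 days. The apparent ratio is 0.96 to 0.92.

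The ratio detectable with 80% power in Table 5 is 0.79. One such infant is negligible against that. Five, all in one arm, would not be.

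**The case against.** The strongest reply is that a PI has little reason to use the clause on a sick infant. *Intervention description* already moves an infant with persistent withdrawal from symptom-based to scheduled dosing while still enrolled, and that transition is itself an endpoint. *Dosing parameters* leaves caregivers discretion to hold doses. The clause also has a coherent use unrelated to outcome: *Potential risks* names loss of confidentiality as a risk of record review, and consent is waived. An adverse event of special interest that is already recorded must still be followed to resolution or stabilisation. Data handling after withdrawal may also be set out in the full protocol, which is not shown.

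Much of this stands, and it rules out several stronger readings that a reader might infer:

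- *That symptom-based dosing will look safer than it is.* Nothing shows that terminated infants would be the worst cases or would come mainly from one approach.
- *That terminated infants stay in the safety denominator while their events drop out of the numerator.* Table 4 says only that percentages are summarised by intervention. It does not say how incomplete follow-up is counted.
- *That the seizure pause rule is compromised.* It pools both approaches and needs more than 1% of infants as well as 7 cases. Nothing indicates that seizures would go unrecorded.
- *That the site PI decides.* The clause says only the PI. The point holds on either reading, since the site PI and the protocol study team are both unblinded.
- *That the clause must be deleted.* It is enough to separate the decision from the end of data collection.

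The reply does not remove the mismatch itself. If the clause is meant for departures from the assigned approach, it says the wrong thing: the parent section's title mentions discontinuing the study intervention, but the text offers only termination from the study.

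**Conclusion.** The point holds as a badly fixed rule, not as a demonstrated bias. The article states a ground for termination that does not change the infant's care, whose natural effect is to end data capture, and that conflicts with safety review of all enrolled infants and with the ITT definition. It permits avoidable, possibly outcome-related loss of later inpatient events and 3-month safety outcomes.

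The size and direction of any bias are unknown, because neither the withdrawal rate nor the handling of terminated infants in the safety percentages is given. If the rule is rarely used, the effect is small. The conclusion assumes that termination from the study ends record review, which is its plain meaning and fits Table 3 but is not stated for the safety outcomes. The change is worth making because the loss is avoidable at almost no cost.

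**What to change.** Reword *Participant stopping rules and withdrawal criteria* so that a PI best-interest decision, or a departure from the assigned approach, is recorded with its date and reason but does not end data collection. State that record review continues to 3 months for every enrolled infant unless the infant dies or the family asks that data not be collected. Table 3's cut at withdrawal would then apply only in those two cases.

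No clinical rule changes, and clinicians' freedom to treat is untouched. No visits or patients are added. The only downside is abstracting the remaining records of the few infants concerned. Because the data are existing records, the clarification could also cover infants already terminated, subject to agreement of the single IRB.
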